**Methods/Design:**

In this five-hospital RCT with long-term follow-up, we aim to recruit *n* = 180 patients in treatment for opioid dependence and allocate them in an open, randomized manner (1:1) to receive either 4-week XR-NTX or daily buprenorphine-naloxone (BP-NLX) for the duration of 12 weeks. Allocation is open-label due to the risk of overdose during attempts to self-unmask allocation using heroin. Urine drug tests are scheduled every week with follow-up visits & assessment every 4 weeks. Primary outcomes are abstinence from illicit opioids in urine drug tests and self-report, as well as retention in treatment. Secondary outcomes include other substance use, injecting behavior, drug craving, mental health, quality of life, treatment satisfaction, abstinence motivation, opioid agonist effect rating, insomnia, and pain. Observation is continued for another 36 weeks in order to assess longer-term safety, adherence and effectiveness. The study is an investigator-initiated trial, funded by public grants and approved by an Independent Ethical Committee (the Regional Ethical Committee for Research South-East B # 2011/1320) and the Norwegian Medicines Agency.

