Despite the dilemmas inherent in treating opioid users with opioid agonists, current guidelines recommend ART due to its ability to retain patients in treatment while greatly reducing illicit opioid use and overdose risk [5]. This in contrast to the other main treatment principle, medication-free abstinence, which is generally not recommended due to the elevated risk of overdose following a period of abstinence from opioid agonists. Despite the risks, treatment based on medication-free abstinence is available in most countries, e.g. as long-term residential treatment or therapeutic communities with outpatient follow-up.

A main concern for opioid addiction treatment is its limited uptake in the user population: Only about 50 % of the patient base are estimated to be in treatment at any one time [5, 13]. The potential human and social benefit of increasing the number of opioid users in treatment is the main incentive to exploring novel treatment approaches.

One recent innovation is sustained release formulations of the opioid antagonist naltrexone [14–16] (SRX). Following detoxification from all opioid agonists (e.g. heroin, morphine, methadone, buprenorphine), naltrexone medication will support the person in avoiding relapse by rendering attempts at relapse futile: as naltrexone competitively blocks the action of heroin and other opioid agonists, the drug euphoria (or ‘high’) as well as sedative effects should effectively be inaccessible to the patient. The only version of SRX currently approved by the FDA, extended release naltrexone (XR-NTX), is administered intramuscularly in the gluteus where it releases naltrexone at therapeutic levels for the duration of 4–5 weeks per injection. XR-NTX appears superior to placebo in both laboratory and clinical settings [17–19]; other sustained release naltrexone (SRX) formulations have shown promising results compared to daily oral naltrexone [20, 21] and to usual-treatment controls [22, 23].

Given the success of ART in clinical practice, a valid policy question is the need to implement another treatment like extended-release naltrexone for the target disorder, opioid dependence. This is best addressed by a randomized controlled trial of long-acting naltrexone with the currently most similar ART medication on offer, daily ART with buprenorphine-naloxone.

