### Research questions and hypotheses

The main research question is whether 4-week XR-NTX will be more effective than–or equally effective to a current standard treatment–daily BP-NLX–on primary and secondary outcomes during or at the end of the 12-Week study.

As an exploratory study with both non-superiority and superiority as plausible scenarios [34] there are two sets of hypotheses for this RCT:

XR-NTX will influence primary and secondary outcomes to be either:statistically superior to assignment to the current standard treatment, ART with daily BP-NLX orstatistically non-superior to ART with daily BP-NLX.

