#### Outcomes & instruments

Urine Drug Test (UDT) data will be analyzed in accordance with recent Cochrane specifications as either a) proportion of total number of UDTs without illicit opioids or b) number of UDTs negative for illicit opioids received from each patient in each group during the 12-week randomized period [37].

Retention in treatment is defined in two ways: Number of days (of maximum 84 days) receiving effective pharmacological treatment, and number of patients completing the study at Week 12.

At baseline and every 4 weeks, patients undergo a structured interview and a selection of patient-reported outcomes: The European version of the Addiction Severity Index (the Europ-ASI) [38, 39] comprises drug and alcohol use, physical and mental health, work, education, social relations, and criminal behavior. The Europ-ASI is used for the second main drug use outcome measure, the number of days of abstinence from illicit opioid use in the 28 days preceding each interview for a total (maximum) of 84 days. To increase accuracy of responses relative to the Europ-ASI standard, timeline follow-back is used: a technique of backtracking and questioning about use and abstinence to obtain as accurate an estimate as possible of total number of days’ use of a specific substance in the 28-day follow-up period [40].

In addition to the primary outcomes, we explore secondary outcomes of importance to recovery: Number of patients fulfilling MINI [36] (DSM-IV) criteria for dependence on illicit opioids (exempting the 12-month criterion). The Addiction Severity Index administered every 4th week also records information on the use/abuse of alcohol, amphetamines, cannabis, sedatives (e.g. benzodiazepines), as well as other illicit substances (e.g. LSD, MDMA, GHB), and poly-drug use; days of injecting drug use; any overdoses (non-lethal) and hospitalizations in somatic or psychiatric health care; workdays and days engaged in illegal activities; number of days with conflicts in close relations, days physical and mental illness.

Craving for heroin is assessed using a 0–10 Visual analogue scale (VAS) on two questions: ‘I need heroin’ where ‘0’ signifies ‘Strongly disagree’ and 10 ‘Strongly agree’; and ‘How much have you been bothered by thinking about opioids or their use in the past 4 weeks?’ with 0 indicating ‘not at all’ and 100 ‘constantly’.

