Mental health is assessed using the 25-item Hopkins Symptom Checklist [41], life satisfaction using the Temporal Satisfaction With Life Scale ‘present’ items [42]. Treatment satisfaction was assessed using a visual analogue scales of 0–10 on the questions ‘How satisfied/dissatisfied are you with having had/not having received XR-NTX in the previous 4 weeks?’ and ‘To what extent would you recommend XR-NTX to a friend who was in the same situation you were in when entering this study?’. Based on previous studies [17, 43] the frequency and euphoria (‘high’) from any illicit opioid use was investigated using visual analogue scales on a qualitative description of any effects, the similarity of the experience to un-blocked drug euphoria (‘high’), what they would be willing to pay for a similar experience had they been in active drug use. In addition, motivation for abstinence using the SOCRATES-8 days [44], and pain assessment using the McGill Pain Questionnaire Short Form [45]. Norwegian language versions are used for all instruments.

Priority will be given to collection of primary outcomes for participants who are assessed to be unable (e.g. due to intoxication) to complete follow-up on one or more visits.

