### Statistical analyses

Statistical analyses on the randomized part of the study will be conducted by a non-study statistician on a final RCT data set in which the two study medications is masked as ‘Rx A’ and ‘Rx B’; any obvious characteristics of the two comparison medications will also be censored before data are made available for analysis. For between- group comparisons and to control for the effect of baseline characteristics, we will use a General Linear Mixed Models (GLMM) approach containing factors for treatment group, sex, and sex-by- treatment interaction, and with age, duration of opioid dependence, and duration of last pre-study inpatient detoxification as covariates. For outcomes violating the normality assumption, a General Alinear Mixed Models (GAMM) approach will be used. Regular statistics (e.g. ANOVA, linear regression) may be utilized if the arguments for using GLMM or GAMM over legacy analysis types are considered to provide limited benefit. Retention will be assessed with Kaplan-Meier curves and a log-rank test. Adverse events will be compared using Fisher’s exact test. The primary endpoints are tested with a two-sided α = 0.05. Where relevant, *p* values will be adjusted for multiplicity using the Bonferroni-Holm method to preserve family-wise type 1 error at 0.05. Once the statistician concludes data analysis of the RCT phase, study management will be able to access the final dataset.

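### The opioid effect ('high') rating exists only for patients who used illicit opioids, so a between-arm comparison of it is open to selection bias and carry-forward imputation does not fit it

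*Protocol article*

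**What the plan says.** The abstract of the protocol article names among the secondary outcomes "treatment satisfaction, abstinence motivation, opioid agonist effect rating, insomnia, and pain". Under 'Outcomes & instruments' the 'high' "from any illicit opioid use was investigated using visual analogue scales on a qualitative description of any effects". One of the scales asks about "the similarity of the experience to un-blocked drug euphoria". The same sentence records how often illicit opioids were used.

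Under 'Research questions and hypotheses', "XR-NTX will influence primary and secondary outcomes to be either" superior or non-superior to BP-NLX. Under 'Statistical analyses', a mixed model is to be used "For between- group comparisons and to control for the effect of baseline characteristics", and no outcome is exempted. Under 'Analysis sets', missing values are filled from the last attended follow-up or, if there was none, from the inclusion data.

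On timing, the outcomes section says "At baseline and every 4 weeks, patients undergo a structured interview and a selection of patient-reported outcomes". 'Outpatient follow-up' says that this visit coincides with re-injection and that each collected dose is registered. The Background says of XR-NTX that "it releases naltrexone at therapeutic levels for the duration of 4–5 weeks per injection". 'Discontinuation' allows re-dosing up to 4 days past day 28 before adherence is broken.

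**The concern.** The rating is conditional on illicit opioid use. Use happens after randomization, and the study drugs are meant to change it. The patients who supply ratings in one arm therefore need not resemble those in the other. A difference in mean rating may reflect who used as well as what the drug did. Adjusting for the listed baseline covariates does not restore the balance that randomization gave.

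The imputation rule adds a second problem. For a patient with no use, the rating is undefined, not missing. Carrying forward an older rating attributes an experience that did not occur. The article does not say whether this item is asked at inclusion. If it is, the rule could place a pre-treatment, unblocked 'high' in the XR-NTX arm.

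A third, smaller point concerns interpretation. The rating is worded as a blockade question, but it covers any use. A use after release has ended would enter the XR-NTX mean as if it had been tested against the blockade.

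**Working it through.** The article gives no sample size, power or expected value for this rating, so there is no figure of its own to reproduce. The steps below give orders of magnitude only.

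**1. Does the set of raters differ by arm on the plan's own assumptions?**

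Inputs ('Determination of sample size'): mean negative samples 7 of 12 (XR-NTX) and 4 of 12 (BP-NLX), SD 3 in both arms, 90 patients per arm. Assumptions added here: every non-negative sample counts as use, and a four-week window holds four weekly samples.

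Beta-binomial, with m the mean proportion negative:
- ρ = (9 / [12·m·(1−m)] − 1) / 11
- a + b = 1/ρ − 1, and a = m·(a + b)
- P(all four negative) = a(a+1)(a+2)(a+3) / [(a+b)(a+b+1)(a+b+2)(a+b+3)]

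| | XR-NTX | BP-NLX |
|---|---|---|
| 12·m·(1−m) | 2.917 | 2.667 |
| ρ | 0.190 | 0.216 |
| P(all four negative) | 0.209 | 0.058 |
| P(any use in four weeks) | 0.791 | 0.942 |
| Raters of 90 | 71 | 85 |

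If weeks were independent, the shares with any use would be 1 − (7/12)⁴ = 88% and 1 − (4/12)⁴ = 99%. Either way the raters are a subset fixed by behaviour after randomization, and the subset differs by arm.

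**2. How large is the selection bias?**

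The simulation has no drug effect on the rating. A latent severity U ~ N(0,1) lowers the chance of a negative sample (the beta quantile at Φ(−U), with a and b from step 1) and raises the rating (5 + slope × U). The slope and the 0–10 range are assumed. There were 300,000 simulated patients per arm.

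| Slope (points per SD) | Mean among users, XR-NTX | Mean among users, BP-NLX | Spurious difference |
|---|---|---|---|
| 0.5 | 5.13 | 5.05 | +0.08 |
| 1.0 | 5.26 | 5.09 | +0.17 |
| 1.5 | 5.39 | 5.14 | +0.25 |

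The bias is not zero, but it is small under these inputs.

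**3. How much XR-NTX time lies outside the release period?**

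Inputs: release 28 to 35 days, re-dosing no later than day 28 + 4 = 32, retention 70% at Week 12.

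- Adherent patient: at most 32 − 28 = 4 uncovered days per interval with 28-day release, and none with 35-day release.
- Patient who stops after injection 1 or 2, 28-day release: 84 − 28 = 56 or 84 − 56 = 28 uncovered days, mean 42.
- Same, 35-day release: 84 − 35 = 49 or 84 − 63 = 21 days, mean 35.
- If the 30% not retained split evenly between these two (assumption), uncovered person-days are 0.30 × 42/84 = 15% or 0.30 × 35/84 = 12.5%.

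If such patients still gave ratings, and ratings followed person-days, the XR-NTX mean would move by 12.5% to 15% of the gap between an unblocked and a blocked rating. The timing problem thus sits almost wholly in late or discontinued patients.

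**The case against.** The strongest reply is that no sentence specifies a between-arm test of this rating. It follows only from general wording on hypotheses and model in a trial that calls itself exploratory, and item-level handling may be left to the full protocol or analysis plan. That lowers the weight of the point but does not remove it. The hypotheses, the model and the imputation rule are stated, and as written they include an outcome they do not fit.

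It is also true that the sound randomized comparison is already planned. Negative urine tests and days of abstinence from illicit opioids are defined for every patient, and frequency of use is recorded beside the rating. A possible per-protocol set would remove most of the timing problem, though not the selection.

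A reader might infer more than the article supports:

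- *That the rating is recalled over four weeks.* The visit interval is four weeks, but no recall window is given for this item.
- *That use is never linked to the last injection.* The article is silent, the case report form is not shown, and registered doses allow at least a visit-level link.
- *That the rating does not measure blockade.* It asks about blockade directly, and adherent patients have at most 4 uncovered days per interval.
- *That ratings after discontinuation will certainly contaminate the XR-NTX arm.* The article does not describe rating visits after a patient has stopped, and it names registries as the source of data on those patients.

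**Conclusion.** The point holds in a limited form. A comparison of arms among users is conditioned on a post-randomization event that the plan itself expects to differ by arm, and carry-forward has no meaning for a patient with nothing to rate. The gap in raters (about 71 against 85 of 90) rests on the plan's own sample assumptions plus the equating of non-negative samples with use. The bias of 0.08 to 0.25 points rests on an assumed severity model and scale; another mechanism could change its size or sign. Within XR-NTX the rating can support a statement about blockade in adherent patients. Ratings from late or discontinued patients may reflect use after release has ended. No primary outcome is affected, and the matter is minor.

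**What to change.** - Keep the planned frequency and abstinence outcomes as the randomized comparison of illicit opioid use.
- Report the effect rating descriptively among users, with the number of raters per arm and visit, and label it a non-randomized comparison.
- Exempt the rating from carry-forward and from filling with inclusion data. Show patients without use as having no rating.
- In XR-NTX, present ratings by time since the last registered injection, linked at visit level through the dose records. Base any statement on blockade on ratings whose interval lies within the stated release period.

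This needs analysis wording and a link to records that already exist. It gives up the between-arm p-value for this rating. Timing will be only at visit level if the date of the rated use was not recorded: timeline follow-back is described as counting days of use, not as dating a rated episode, and recruitment is given as ending in July 2015, so a new date field would come too late for most patients.

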#### Registry data follow-up

The informed consent and Regional Ethical Board approval permits collection of registry linkage data based on the participants’ unique Personal Identity Number given to every permanent resident or employee in Norway upon birth or first residential/employment visa. The PIN is necessary for personal identification to public authorities and to open a Norwegian bank account. The PIN is also used in many registries and makes it possible to link information on individuals across registries [46]. Ethical Board approval has been granted to collect registry data for the study period and up to 1 year before, during and after participation in order to: a) compare data and events occurrence within the group and compare with other groups of interest and b) obtain data on patients who discontinue XR-NTX treatment. Data from the following registries will be included: The Cause of Death Registry, the Norwegian Prescription Database (NorPD), the Police Registry, the Norwegian Prison Registry and the Norwegian Patient Registry (NPR).

### Statistical analyses

Statistical analyses on the randomized part of the study will be conducted by a non-study statistician on a final RCT data set in which the two study medications is masked as ‘Rx A’ and ‘Rx B’; any obvious characteristics of the two comparison medications will also be censored before data are made available for analysis. For between- group comparisons and to control for the effect of baseline characteristics, we will use a General Linear Mixed Models (GLMM) approach containing factors for treatment group, sex, and sex-by- treatment interaction, and with age, duration of opioid dependence, and duration of last pre-study inpatient detoxification as covariates. For outcomes violating the normality assumption, a General Alinear Mixed Models (GAMM) approach will be used. Regular statistics (e.g. ANOVA, linear regression) may be utilized if the arguments for using GLMM or GAMM over legacy analysis types are considered to provide limited benefit. Retention will be assessed with Kaplan-Meier curves and a log-rank test. Adverse events will be compared using Fisher’s exact test. The primary endpoints are tested with a two-sided α = 0.05. Where relevant, *p* values will be adjusted for multiplicity using the Bonferroni-Holm method to preserve family-wise type 1 error at 0.05. Once the statistician concludes data analysis of the RCT phase, study management will be able to access the final dataset.

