#### Determination of sample size

In compliance with current recommendations for non-superiority trials [34], a minimum sample size has been estimated for two scenarios:

The superiority scenario assumes that XR-NTX participants will have opioid-negative samples on a mean of 7 out of the total 12 (7/12 or 0.58) samples, while participants receiving buprenorphine-naloxone will display a mean of 4 opioid-negative samples (4/12 or 0.33). With a 95 % significance level (*p* < 0.05) and a standard deviation of 3 in both medication groups, and power (beta) set to 90 %, a sample size of 17 patients/medication arm or *n* = 34 total is estimated to be sufficient for analysis. The estimated frequency of opioid use in each group is based on data from Norwegian patients receiving sustained release naltrexone [22] or on the frequency of illicit opioid use during buprenorphine maintenance in the Norwegian national ART program.

In the non-superiority scenario, using a beta of 90 %, we assume that both groups will retain 70 % of their participants at the end of Week 12 and set 20 % as the non-superiority margin; this yields a minimum sample size of *n* = 58 in each group/*n* = 116 total.

Based on the sample size calculations and the risk of dropout of a significant proportion of participants, we have set the recruitment target for *n* = 180 total, or *n* = 90 for each medication group. This will be facilitated by characteristics of design (few exclusion criteria, open-label allocation, outpatient data collection often coinciding with medication and counseling), prioritization of amount–and types of data collected. Information about the study will be distributed at clinical sites as well as outreach -, housing- and criminal justice facilities and the internet; these efforts are anticipated to attract the initial *n* = 30 patients whose presence in the larger community of opioid users will be sufficiently inform more potential participants to contact study staff for information.

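### The only method named for retention, a primary outcome, is an unadjusted log-rank test, which forgoes precision that baseline data already recorded may supply

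*Protocol article*

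**What the plan says.** The protocol article's abstract names retention in treatment as a primary outcome beside abstinence by urine test and by self-report. Outcomes & instruments defines retention in two ways: days on effective treatment, up to 84, and the number of patients completing Week 12.

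Statistical analyses gives the general approach: "to control for the effect of baseline characteristics, we will use a General Linear Mixed Models (GLMM) approach". The model has treatment, sex and their interaction as factors, and age, duration of dependence and length of the last inpatient detoxification before the study as covariates. It allows ANOVA or linear regression instead where the mixed models are thought to add little. For retention it says: "Retention will be assessed with Kaplan-Meier curves and a log-rank test". No covariate or stratum is attached. It adds: "The primary endpoints are tested with a two-sided α = 0.05".

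Determination of sample size treats retention as a difference in Week-12 proportions. It assumes that "both groups will retain 70 % of their participants at the end of Week 12 and set 20 % as the non-superiority margin", and "this yields a minimum sample size of *n* = 58 in each group/*n* = 116 total". For the urine-test scenario, "a sample size of 17 patients/medication arm or *n* = 34 total is estimated to be sufficient for analysis". The recruitment target is 90 per group. Randomization states that allocation is independent of site, setting and gender.

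**The concern.** The section states an aim of controlling for baseline characteristics and then gives one primary outcome a named method that does not do so. That outcome has the larger required sample size of the two scenarios. Baseline variables that might predict retention are collected anyway, and allocation is not stratified by sex or setting, so the design does not remove chance imbalance in them. If those variables do predict who stays in treatment, an unadjusted comparison has a wider confidence interval than the same data could give. At stake is power against the 20-point margin.

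**Working it through.** **Inputs.** From Determination of sample size: 70% retained in both arms, margin 0.20, intended power 90%, target 90 per arm. From Statistical analyses: two-sided alpha 0.05. I read the article's non-superiority margin as a limit on how much worse retention may be, judged by one end of a two-sided 95% CI (one-sided 0.025). Patients who leave treatment count as not retained, so all 90 per arm enter the comparison. The prognostic strength of the covariates is not in the document and is assumed over a range.

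**The plan's own figure.** The scenario opens with "In the non-superiority scenario, using a beta of 90" per cent, which I take to mean power.

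n per arm = [0.7(0.3) + 0.7(0.3)] × (1.960 + 1.282)² / 0.20² = 0.42 × 10.51 / 0.04 = 110.3, so 111.

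At one-sided 0.05 the result is 90. The stated 58 is not reproduced at 90% power by any non-inferiority form tried; at 58 per arm the power is 65% (one-sided 0.025) or 76% (one-sided 0.05). That is a separate matter, used here only to show that retention has no spare power.

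**Unadjusted power at 90 per arm.** SE = √(0.42/90) = 0.0683. Power = Φ(0.20/0.0683 − 1.960) = Φ(0.968) = 83.3%.

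**Adjusted power by formula.** If baseline covariates explain a share R² of the variance in retention, SE = √(0.42(1 − R²)/90). For R² = 0.10, SE = 0.0648 and power = Φ(3.086 − 1.960) = 87.0%.

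| R² (assumed) | Power | Gain, points (from unrounded values) |
|---|---|---|
| 0.02 | 84.1% | 0.7 |
| 0.05 | 85.2% | 1.8 |
| 0.10 | 87.0% | 3.7 |
| 0.15 | 88.8% | 5.5 |
| 0.20 | 90.5% | 7.2 |

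**Adjusted power by simulation.** The same scenario was simulated with a logistic model on treatment and five baseline covariates, standardised to a risk difference with an influence-function SE corrected for degrees of freedom, against the unadjusted Wald difference. Runs used 3,000 or 4,000 trials per setting.

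| c-statistic (assumed) | Unadjusted | Adjusted | Gain, points |
|---|---|---|---|
| 0.50 | 83.3% | 82.8% | −0.5 |
| 0.555 | 82.4% | 82.3% | −0.1 |
| 0.60 | 83.6% | 84.0% | 0.4 |
| 0.63 | 82.8% | 84.0% | 1.2 |
| 0.657 | 82.8% | 83.7% | 0.9 |
| 0.69, run 1 | 82.6% | 86.4% | 3.8 |
| 0.69, run 2 | 83.6% | 86.6% | 3.0 |
| 0.765 | 82.9% | 89.5% | 6.6 |

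A further run gave gains of about 0 at 0.50, 1 at 0.58 to 0.64, 2.5 at 0.69 and 6.5 at 0.76. Each simulated power has a Monte Carlo error of about √(0.83 × 0.17/3000) = 0.7 points, so gains below one point should not be read closely.

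**Does the form of adjustment matter?** Yes. In simulated trials of 90 per arm, an adjusted Cox model gave no gain with equal 70% retention and a hazard-ratio margin: unadjusted against adjusted, 69.5% v 68.9%, 68.4% v 67.5% and 68.5% v 67.7% as R² rose through about 0.02, 0.07 and 0.145. With a true difference of 70% v 50%, adjusted Cox did gain in a superiority test: about 79% v 80%, 79% v 83% and 81% v 88%. In the scenario used for sizing, the gain therefore comes from an adjusted risk difference, not from adding covariates to a hazard model.

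**The case against.** Kaplan-Meier with a log-rank test is a standard, valid and pre-stated analysis of time in treatment, and nothing in the article contradicts it. A supportive adjusted model could well sit in an analysis plan that is not shown. The general sentence on between-group comparisons may also cover days on treatment, so the log-rank test need not be the only retention analysis. The power figures above compare two risk-difference analyses, whereas the named test is a log-rank test, for which the article states no power. With weak covariates the gain is nil.

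Most of this stands. It makes the point a missed improvement and not an error. What remains is that the article itself states the aim of baseline control, itself names the retention method, and attaches no covariates to it. It also sizes retention on a difference in proportions, which is the quantity the risk-difference comparison addresses. The change proposed here adds to the log-rank test and does not replace it.

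**Conclusion.** The point holds as a modest loss of efficiency. At 90 per arm the gain forgone is about 0 to 1 points of power for weak covariates (c up to about 0.64), 2 to 4 at about 0.69 and 6 to 7 at about 0.76, on a base of about 83%. It rests on 70% retention in both arms, the 20-point margin, a two-sided 95% CI and an assumed prognostic strength. The simulations used five covariates; a different list matters mainly through the c-statistic it reaches.

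A reader might infer four stronger things that the document does not support:

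- **That retention is the only primary outcome analysed without covariates.** The clause allowing ANOVA or linear regression means that adjustment of the abstinence outcomes is not guaranteed either.
- **That several points of power are lost for certain, and at no cost.** Nothing in the article shows that sex, age, duration of dependence and detoxification length predict retention well enough.
- **That adjustment leaves the estimand as planned.** This is true against the sample-size section, but not against the log-rank test, which compares the whole 84 days.
- **That chance imbalance biases the result.** Under randomisation it is covered by the error rate of the test; it costs precision only. Setting is also a doubtful predictor to press for, since the Discussion reports that recruiting a large share from criminal justice was not feasible.

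**What to change.** Keep the Kaplan-Meier curves and log-rank test for time in treatment. Add, as the Week-12 retention comparison, a logistic model with treatment and the baseline variables that Statistical analyses already lists: sex, age, duration of dependence and length of the last inpatient detoxification before the study. No sex-by-treatment term is needed. Standardise the model over all randomised patients to a marginal risk difference with a robust 95% CI, and read that interval against the 20-point margin. Show the unadjusted difference beside it.

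Take each covariate as it stood at allocation, since tapering continues after allocation in the naltrexone arm. Fix the list in writing before the masked data set is released.

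The cost is a paragraph of wording and a few lines of code, with no new data. The downside is slightly more modelling to explain, and little or no gain if the covariates predict poorly. A side benefit is that this comparison yields a confidence bound on the scale of the margin, which a log-rank test does not.
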